**Methods:**

This prospective cohort will include a population of adolescents and young adults, aged 15 to 30 years old, with ultra-high-risk of psychosis (UHR), first-episode psychosis (FEP), schizophrenia (SCZ), autism spectrum disorder (ASD), and major depressive disorder (MDD), as well as healthy controls (CTRL) (*N* = 21 × 6), who will be assessed at baseline and after one year of follow-up. Participants will undergo deep phenotyping based on psychopathology, neuropsychological assessments, 64-channel EEG recordings, and biological sampling at the two timepoints. At baseline, the EEG recording will also be coupled to a sensorimotor task and a recording of the characteristics of their speech (prosody and turn-taking), a one-night polysomnography, a self-reference effect task in virtual reality (only in UHR, FEP, and CTRL). An interventional ancillary study will involve only healthy controls, in order to assess whether light hypnosis can modify the EEG microstate architecture in a direction opposite to what is seen in disease.

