## Methods

### Participant recruitment

All participants will be included at the Clinical Research Centre (CRC), University Hospital Group Paris Psychiatry and Neurosciences (GHU). Inclusion criteria are: an age between 15 and 30 years old; French as the maternal language or spoken in the context of bilingualism; a DSM-5 diagnosis of schizophrenia or major depressive disorder or autism spectrum disorder; a diagnosis of ultra-high-risk of psychosis or first-episode psychosis based on the Comprehensive Assessment of at risk mental state (CAARMS) translated in its French version [77]; and healthy control subjects recruited from the general population. Exclusion criteria are: suicidal risk; severe or non-stabilized somatic and neurological disorders; epilepsy; head trauma; IQ below 70; presence of other psychiatric disorders (bipolar disorder, obsessive–compulsive disorder, or substance use disorders, except for tobacco or cannabis, tolerated up to 5 joints/day); for healthy control subjects, a family history of psychosis is an exclusion criterion. Pregnant or breast-feeding women will not be included.

Participants will be screened among the population of patients seen at an early psychosis outpatient clinic (Centre d’évaluation des jeunes adultes et adolescents—CJAAD, GHU). Healthy controls will be reached through the healthy volunteers database of the CRC. Participant assessment will be as follows (Fig. 1, Table 1). 1) During the pre-inclusion visit, participants will be informed of all the details of the protocol, orally and in writing, and eligibility criteria will be verified. Then a two-week reflection period will be observed, before the signature of a written consent at the baseline inclusion. 2) The baseline visit will consist of a first visit of three half-day sessions including medical, psychopathological and neuropsychological assessments, biological sampling (described below), and speech recording. In the following two months, participants will undergo one night of polysomnography (everyone) and two half-day sessions for the sensorimotor task (everyone) followed by light hypnosis (only controls), and the self-reference effect task in virtual reality (only controls, UHR, and FEP). 3) The follow-up visit will consist of a second psychopathological and neuropsychological assessment, biological sampling, and shorter EEG recording (5–10 min).

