### Sensorimotor integration task

Sensorimotor integration is investigated using a visuo-tactile task. On each trial, the participant, seated in front of a screen, has a visual instruction: a point to the right or left of the screen. The task consists of pressing one of the two buttons positioned on each side of the body with the index finger of the corresponding hand according to the visual instruction. A vibrotactile stimulator (small bone conduction speakers wired to an Arduino electronic card modulated by an amplifier) is applied to the first dorsal interosseous muscle of both hands. 400 msec before the visual instruction, one of the two hands receives a tactile cue (vibration) on one hand for 100 msec. The tactile cue can be congruent or incongruent with the visual cue, both indicating or not the same hand. Depending on the block, the tactile cue can be more or less reliably coupled with the visual stimulus. In *reliable* blocks, 90% of the trials present the vibration and visual instruction congruently (indicating the same hand). In *non-reliable *blocks, only 50% of the trials are congruent, and in this case, the tactile cue is not reliable. Two blocks with 70% congruent cases are carried out intermediately. Finally, a baseline block which does not contain any tactile cues is presented at the beginning and the end of the task. The order of the 90% and 50% blocks is randomized. The tactile and visual stimuli are generated with a MATLAB script. Each block consists of 100 trials, in total 500 trials. EEG data is recorded throughout the task, using a 64-channel EEG cap (from Biosemi). The setup is coupled to an eye tracker in order to control that the participant is fixing the cross at the center of the screen during each block. At the end of the task, a five minute eyes closed resting-state EEG will also be recorded. In order to examine attentional modulation, measurement of alpha power band (in Hz) is computed. Cortical excitability and inhibition are analyzed with mu and theta bands (in Hz), and integration of sensory information as somatosensory evoked potentials (SEPs), where amplitudes (in µV) and latencies (in msec) are extracted. The adaptation of the reaction time (in msec) to the button press according to the probabilistic context of congruency is examined. Analysis is conducted with Python scripts with dedicated libraries such as MNE-Python [84]. This task has been designed and will be supervised by researchers trained in neurophysiology recording and analysis (AA, LD).

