
### Hypnosis task

After the sensorimotor integration task, healthy controls will undergo a light hypnosis task coupled with two control tasks, in addition to the eyes-closed resting-state already recorded. First, participants will be asked to listen to a neutral text (a refrigerator manual) read by the investigator, with the instruction to listen attentively in order to be able to answer specific questions regarding the content of text. Second, participants will do a mental calculation test. Third, participants will undergo the light hypnosis task. Light hypnosis is based on Ericksonian hypnosis without inducing a trance state, and has been developed by the Collège International des Techniques par Activation de la Conscience (CITAC; [name], [name]) as part of the Paris-Saclay university training in clinical hypnosis. Participants will be asked to focus on any type of preoccupation they may have, and then to picture the first step towards resolving this preoccupation. They will then be asked to provide resources or qualities they have. The light hypnosis session will then start by asking the participant to assume a comfortable and at the same time tonic position, sitting straight, the back lifted from the chair. They will be asked to close their eyes, while being informed that they can open them at any time if needed. They will then be asked to picture their objective, and the first step toward its solution. Then, they will be asked to picture themselves in a situation where they learnt to do something. Proprioceptive, sensory (each of the five senses), and metaphorical suggestions based on their resources will be provided in order to guide the participant in this exercise. This task has been designed and will be performed by two psychiatrists trained in clinical hypnosis (AI, CLo).

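### The only baseline resting EEG described follows the sensorimotor task and the one-year EEG apparently does not, so within-person change in resting microstates is aliased with task after-effects

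*Protocol article*

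**What the plan says.** The Sensorimotor integration task section puts the resting recording after the task: "At the end of the task, a five minute eyes closed resting-state EEG will also be recorded". On task length it says: "Each block consists of 100 trials, in total 500 trials". The Hypnosis task section then relies on that same recording, describing the hypnosis and control conditions as coming "in addition to the eyes-closed resting-state already recorded". No rest before the task is described anywhere in the text.

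The Methods paragraph of the abstract places the task at the first timepoint ("At baseline, the EEG recording will also be coupled to a sensorimotor task") and says that participants have "64-channel EEG recordings, and biological sampling at the two timepoints". Under Participant recruitment, the waking EEG belongs to the "two half-day sessions for the sensorimotor task (everyone) followed by light hypnosis (only controls" that come within two months of the baseline visit. In the same section the follow-up visit consists of clinical and neuropsychological reassessment, "biological sampling, and shorter EEG recording (5–10 min", with no task listed.

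The Microstates analysis section derives microstates from eyes-closed rest, from the task and from sleep. The Objectives section frames the microstate comparison over two timepoints a year apart, and the Statistical analysis design section plans a repeated measures ANOVA with between-group contrasts.

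**The concern.** The task and the polysomnography are described only at baseline, so rest is the only state in which microstates can be compared across the two visits. If baseline rest always follows several hundred button-press trials and one-year rest follows none, each participant's change score is the sum of true one-year change and the loss of any task after-effect, such as fatigue, drowsiness or sensorimotor carry-over. The two always occur together, so neither a covariate nor a larger sample can separate them.

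At stake is the reading of within-group change as disease course. A group-by-time result is also at stake if patients and controls carry over differently from the task. The protocol's own hypotheses make carry-over plausible: the Background and Discussion link microstate class E to sensorimotor processing, and the Discussion expects altered attentional and inhibitory responses in psychosis.

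**Working it through.** **Recording conditions side by side**

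- Baseline: five minutes, eyes closed, after the task. The stated total is 500 trials. The blocks listed (90%, 50%, two at 70%, and a no-cue block at the beginning and the end) come to 6 × 100 = 600. That discrepancy is a separate matter, since either count puts hundreds of trials before the rest.
- One year: 5–10 minutes. No task is listed and the eye state is not stated.
- Could the task fit into the one-year recording? Ten minutes less five minutes of rest leaves 300 s, and 300/500 = 0.6 s per trial. The tactile cue alone precedes the visual instruction by 0.4 s. A task-free follow-up is therefore the reasonable reading.

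**Model**

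Let D be the true one-year change and A the task after-effect present at baseline only. Observed change = D − A.

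- Within one group, or as a main effect of time, D and A cannot be separated.
- Patients minus controls: (D_p − D_c) − (A_p − A_c). If A_p = A_c, the after-effect cancels.
- Baseline group contrast: true difference + (A_p − A_c). It too is affected only if the after-effects differ.

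**The plan's own figure**

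The plan gives no figure for the after-effect. Its sample size reproduces: a one-way ANOVA with 6 groups, effect size 0.5 and alpha 0.05 needs 15 per group for 95% power (power 0.962 at 15 and 0.948 at 14). At 21 per group the power is 0.996. Only the total of 126 and the split into 5 × 21 = 105 patients and 21 controls are used below.

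**Illustration 1: common after-effect, main effect of time**

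Assumptions: no true change, all 126 retained, a shift of 0.2 SD of the raw measure, two-sided 5% test. SE of the mean change = √(2(1−r))/√126, in SD units, where r is the within-person correlation (assumed).

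- r = 0.5: SE = 0.089, z = 2.24, rejection about 61%
- r = 0.6: SE = 0.080, z = 2.51, rejection about 71%
- r = 0.7: SE = 0.069, z = 2.90, rejection about 83%

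In a single group of 21, a shift of 0.2 SD of the change score gives 14%.

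**Illustration 2: differential after-effect, patients against controls**

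In SD units of the change score (the same as raw SD when r = 0.5), SE = √(1/105 + 1/21) = 0.239. Noncentral t rejection rates:

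- difference 0: 5%
- 0.1: 7%
- 0.2: 13%
- 0.3: 24%
- 0.5: 55%

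Dropout would lower these rates without reducing the bias.

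**The case against.** The strongest reply is that little of the planned analysis is exposed. Every contrast listed in the Statistical analysis design section is between groups, a main effect of time is not among them, and all groups follow the same schedule. A reader might infer that any time or group-by-time result is confounded, and lead with the 61–83% range. The documents do not support that: a common after-effect cancels between groups, and that range applies only to a test that is not listed.

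A reader might also infer that the baseline diagnostic contrasts are confounded with fatigue. They are post-task comparisons, but standardised ones, and nothing in the documents shows that the after-effect differs by diagnosis. Nor does EEG change carry the whole longitudinal question, since prognosis can be studied from baseline microstates and one-year clinical and functional outcome.

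The difference in recording length is mostly handled. Occurrence per second, coverage in percent and mean duration are normalised for length, and each subject contributes the same number of GFP peaks to the clustering. Only drowsiness late in a longer recording remains.

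Finally, the article is condensed, Table 1 and Fig. 1 are not shown, and no sentence says that the follow-up is task-free or that there is no pre-task rest.

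These points stand, and they limit the finding. They do not remove the mismatch in the text as written, or its effect on within-person change.

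**Conclusion.** The concern holds in a limited form. As described, resting conditions differ between the two visits in every participant, so within-person one-year change in resting microstates, and any main effect of time, cannot be read as disease course. Group-by-time and baseline contrasts are biased only to the extent that the after-effect differs between groups, which is plausible but not quantified.

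The size is unknown. The after-effects and correlations above are assumptions, and full retention is assumed throughout. Over a differential of 0.1–0.5 SD of the change score, the false-positive rate for the patient–control group-by-time contrast runs from 7%, close to nominal, to 55%. The upper end assumes a difference numerically as large as the 0.5 that the power section takes as its minimum effect size, and nothing in the documents supports an after-effect that large.

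The conclusion rests on reading the follow-up EEG as task-free and the post-task rest as the only baseline rest. Confidence in that reading is moderate to good. This is an inexpensive improvement to the two-timepoint comparison and does not invalidate the study.

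**What to change.** - At baseline, record five minutes of eyes-closed rest before the first task block, with the cap already on, and name it as the baseline for the longitudinal resting comparison.
- At one year, record rest with the same eye state and instructions, and analyse the same length. State these conditions in the text.
- Keep the post-task rest as the reference for the hypnosis ancillary study.
- For participants who have only post-task rest at baseline, do not interpret within-group change or the main effect of time as disease course. The missing recording cannot be recovered later.
- If the full protocol already includes a pre-task rest, one sentence naming it as the longitudinal measure is enough.

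The cost is about five more minutes in an existing session and a change to the procedure manual. Sample size and the listed contrasts are unaffected.

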
### Hypnosis task

After the sensorimotor integration task, healthy controls will undergo a light hypnosis task coupled with two control tasks, in addition to the eyes-closed resting-state already recorded. First, participants will be asked to listen to a neutral text (a refrigerator manual) read by the investigator, with the instruction to listen attentively in order to be able to answer specific questions regarding the content of text. Second, participants will do a mental calculation test. Third, participants will undergo the light hypnosis task. Light hypnosis is based on Ericksonian hypnosis without inducing a trance state, and has been developed by the Collège International des Techniques par Activation de la Conscience (CITAC; [name], [name]) as part of the Paris-Saclay university training in clinical hypnosis. Participants will be asked to focus on any type of preoccupation they may have, and then to picture the first step towards resolving this preoccupation. They will then be asked to provide resources or qualities they have. The light hypnosis session will then start by asking the participant to assume a comfortable and at the same time tonic position, sitting straight, the back lifted from the chair. They will be asked to close their eyes, while being informed that they can open them at any time if needed. They will then be asked to picture their objective, and the first step toward its solution. Then, they will be asked to picture themselves in a situation where they learnt to do something. Proprioceptive, sensory (each of the five senses), and metaphorical suggestions based on their resources will be provided in order to guide the participant in this exercise. This task has been designed and will be performed by two psychiatrists trained in clinical hypnosis (AI, CLo).

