### Objectives of the DEMETER study

Building on our preliminary results, the DEMETER project (“Détermination Des Microétats EEG associés Aux Troubles Psychiques Dans Les États à Risque”—EEG Microstates Across At-Risk Mental States) is a prospective observational study that aims to characterize the EEG microstate signature with regard to underlying neurophysiological functions, including sensorimotor integration, speech, sleep, and sense of self, across a population of adolescents and young adults, with ultra-high-risk of psychosis (UHR), first-episode psychosis (FEP), schizophrenia (SCZ), autism spectrum disorder (ASD), and major depressive disorder (MDD), compared with healthy controls (CTRL) (*N* = 21 × 6), between two timepoints one year apart.

Participants will undergo deep phenotyping based on psychopathology and neuropsychological assessments at baseline and after one year of follow-up, high-resolution EEG (64 electrodes) with a resting period and a sensorimotor task, a recording of the characteristics of their speech (prosody and turn-taking), a one-night polysomnography, and biological sampling for multi-omic analyses, and a self-reference effect task in virtual reality (the latter only in UHR, FEP, and CTRL).

The main questions it aims to answer are as follows. 1) Are EEG microstate anomalies associated with specific disorders, and clinical and functional prognosis, both in resting conditions and during sleep ? 2) Are EEG microstate anomalies associated with differences in sensorimotor integration, speech, and sense of self ? 3) An interventional ancillary study will involve only healthy controls, in order to assess whether light hypnosis conditions can modify the EEG microstate architecture in a direction opposite to what is seen in disease.

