### Microstates analysis

Microstate analysis will be performed on eyes-closed resting-state, during the sensorimotor integration task, and during sleep. A minimal preprocessing will be done with the MNE EEG software on Python, which includes a bandpass filter between 0.5 and 40 Hz, rereferencing to the mean, and visual and automatic correction for artifacts using independent component analysis (ICA). Each recording will be visually reanalyzed by clinical neurophysiologists to check for any residual artifact. Microstate analysis will be done using the Pycrostates package [91]. Global field power (GFP) will be determined for each participant. Only EEG topographies at GFP peaks will be retained to determine microstates’ topographies, through a modified K-means clustering. For each subject the same number of GFP peaks will be extracted and concatenated into a single data set for clustering. A combined score will be used to compute the optimal number of clusters. The resulting clusters will be backfitted to each individual maps. Temporal smoothing will be used to ensure that periods of inter-peak noise, of low GFP, did not interrupt the sequences of quasi-stable segments. For each subject, three parameters will be computed for each microstate class: frequency of occurrence (“occurrence”), temporal coverage (“coverage”) and mean duration. Occurrence is the average number of times a given microstate occurs per second. Coverage (in %) is the percentage of total analysis time spent in a given microstate. Mean duration (in ms) is the average time during which a given microstate was present in an uninterrupted manner (after temporal smoothing).

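### In the ancillary hypnosis study all controls follow one fixed order with hypnosis last and no closing rest, so a microstate change under hypnosis cannot be separated from time on task; separately, the microstate section omits these recordings

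*Protocol article*

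**What the plan says.** The sequence for healthy controls is set out in two sections of the protocol article.

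- Sensorimotor integration task: 500 trials, then rest. "At the end of the task, a five minute eyes closed resting-state EEG will also be recorded".
- Hypnosis task: the rest just mentioned serves as one comparison, and three conditions follow in numbered order. "First, participants will be asked to listen to a neutral text (a refrigerator manual) read by the investigator". "Second, participants will do a mental calculation test". "Third, participants will undergo the light hypnosis task".

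No random or counterbalanced order, no rest after hypnosis and no group of controls without hypnosis is described. Other tasks in the same article do have order control: the 90% and 50% sensorimotor blocks are randomised, and the virtual-reality conditions are counterbalanced.

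The Objectives section asks whether hypnosis "can modify the EEG microstate architecture in a direction opposite to what is seen in disease". The Abstract lists modulation by hypnosis as the third main question, and the Discussion calls it a proof of concept.

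The Microstates analysis section names its recordings: "Microstate analysis will be performed on eyes-closed resting-state, during the sensorimotor integration task, and during sleep". Hypnosis, listening and calculation are not among them.

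**The concern.** There are two distinct points.

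The first is design. The hypnosis question is causal: does the intervention change the microstates? Each condition has exactly one position in the session, the same for everyone. Fatigue, drowsiness or changing electrode contact could each shift microstate parameters over the session, and such a shift would look like an effect of hypnosis. No analysis after the recordings are made can undo this, because the information was never collected.

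The second is consistency. The third main question needs microstates computed under hypnosis, but the section that says where microstates will be computed does not include it. This has no bearing on the confounding. It is a mismatch between an objective and the methods.

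**Working it through.** **The plan's own figure.** The article's only sample size is for a six-group ANOVA with effect size 0.5, alpha 0.05 and power 95%. From the noncentral F distribution with k = 6 and f = 0.5, power is 0.948 at n = 14 and 0.962 at n = 15, so the stated 15 per group reproduces. At the planned 21 per group it is 0.996. This figure does not size the hypnosis comparison, but it fixes the number of controls at 21.

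**Can the effect be estimated?** Number the positions: rest 0, listening 1, calculation 2, hypnosis 3. Take a model with an intercept, three condition effects and a linear position term, which is 5 parameters.

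- Order as planned: four distinct rows, rank 4 of 5. The hypnosis effect and drift are not separately estimable, whatever the number of controls.
- With a closing rest at position 4: rank 5 of 5. Estimable.
- With the three tasks counterbalanced over their six orders: rank 5 of 5. Estimable, if there is no carry-over.

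The control tasks would identify drift only if listening and calculation themselves leave microstates unchanged, which nothing in the document supports.

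**How large could the error be?** Inputs: n = 21 (Statistical power estimates); two-sided alpha 0.05. Assumptions, none in the document: no true hypnosis effect, no effect of listening or calculation, drift D of 0.2 to 0.5 SD between rest and hypnosis, within-person correlation r of 0.5 or 0.7 between any two conditions.

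*Hypnosis minus rest.* Mean difference D, SD = √(2(1 − r)), which is 1.000 at r = 0.5 and 0.775 at r = 0.7. Noncentrality = D√21 / SD, with 20 degrees of freedom and critical t = 2.086. Example: D = 0.3 and r = 0.5 gives 0.3 × 4.583 / 1.000 = 1.375.

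*Hypnosis minus the mean of listening and calculation.* With linear, equally spaced drift the two tasks carry D/3 and 2D/3, mean D/2, so the difference carries D − D/2 = D/2. Its variance is 1 + 1/2 + r/2 − 2r = 1.5(1 − r), so the SD is 0.866 or 0.671.

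Share of studies that reject when hypnosis does nothing:

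| Drift D | vs rest, r = 0.5 | vs rest, r = 0.7 | vs mean of controls, r = 0.5 | vs mean of controls, r = 0.7 |
|---|---|---|---|---|
| 0.2 | 14% | 20% | 8% | 10% |
| 0.3 | 26% | 39% | 12% | 16% |
| 0.5 | 59% | 80% | 24% | 37% |

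With no drift, every column is 5%.

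**The case against.** - **The control tasks deserve credit.** It is tempting to say that all drift falls on hypnosis. It does not: rest, listening and calculation occupy successive earlier positions, drift builds up across all four, and a steady trend might be visible before hypnosis starts. This stands, and it is why the rates against the control tasks are much lower than against rest. It does not remove the confounding, because position and content change together at each step.
- **The rates are assumed.** Neither drift nor correlation is in the document, and drift during the 500 trials does not enter a comparison that starts at the later rest. This stands. The table shows sensitivity and does not predict an error rate. The objective is also directional, so drift would mimic the hoped-for result only if it ran in that direction. The rank result needs none of these values.
- **Hypnosis last may be deliberate.** It protects the control tasks from carry-over. That is a defensible choice, so full randomisation is not clearly better. It does not explain the lack of a closing measure.
- **An article condenses.** A reader might also fault the unstated eye condition in the control tasks or the lack of a named hypnosis contrast in the statistical section. Both may be settled in a fuller document, so neither is a finding. The numbered order and the list of recordings, by contrast, are stated outright.
- **The study is ancillary.** It is limited to healthy controls and described as a proof of concept. This limits the weight of the point, though the Abstract still counts it among three main questions.

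**Conclusion.** The point holds for the ancillary hypnosis study only. With one fixed order, no closing rest and no group without hypnosis, the effect of hypnosis and time on task are not separately estimable (rank 4 of 5 parameters). That conclusion depends only on the stated order. Its practical size depends on assumed drift: for 0.2 to 0.5 SD and r of 0.5 to 0.7, false rejection is 14% to 80% against rest and 8% to 37% against the mean of the control tasks, the latter under linear, equally spaced drift.

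The omission from the microstate list is a separate inconsistency with the third main question. A reader might infer that it contributes to the confounding, or that the hypnosis recordings will not be analysed at all. The document supports neither: the list does not bear on order, and the stated objective shows the analysis is intended.

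Comparisons between diagnostic groups do not use the hypnosis recordings and are unaffected. This is a worthwhile, inexpensive improvement and not a flaw in the main study.

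**What to change.** 1. Keep hypnosis last and add a five-minute eyes-closed rest after it. Compare hypnosis with the two rests that bracket it, interpolated to the time of hypnosis. A plain average of the rests is not enough: with equal spacing they sit at positions 0 and 4, mean 2, while hypnosis is at 3, so one step of drift (D/3) would remain.
2. State in advance how an after-effect is handled. The change from first to closing rest is drift plus any after-effect of hypnosis, and the two cannot be split. A change that does not return to baseline must therefore be reported as ambiguous.
3. Add the hypnosis, listening and calculation recordings to the list in the Microstates analysis section.

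The cost is five more minutes of recording for each of 21 controls and one amended sentence.

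Counterbalancing listening, calculation and hypnosis over their six orders (3 or 4 controls each) is an alternative only if carry-over from hypnosis is judged negligible. A period term in the model adjusts for position and does not test carry-over.
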